### The intervention

#### General goals of the interventions

The intervention evaluated in this trial consists of several components as summarised in Table 1. All components are based on the principles of risk and problem identification, achievement of favourable behaviour changes in older persons, and facilitation of preventative care use. The intervention consists of a written component (HRA-O questionnaire and feedback reports to older persons and providers) and personal patient education using multiple modalities with involvement of GPs and other health care professionals.

**Table 1 T1:** Description of the HRA-O intervention as implemented in the PRO-AGE study

**Aspect of the intervention**	**Description**
General goals of the	To identify risks for functional decline and problems
intervention	To achieve favourable change in health-related behaviour
	To facilitate preventative care use
Training of health professionals	Use of a specially prepared manual as a basis for training of GPs and additional health professionals involved in the intervention (copy available, see additional available material)
	Initial and follow-up training of GPs and additional health professionals involved in the intervention in groups, led by one of the project physicians trained in preventative geriatric medicine
Use of HRA-O instrument	Mailing of HRA-O questionnaire to participants (copy available, see reference No. 7)
	Written individualised participant feed-back report
	Written provider HRA-O summary feed-back report
Personal reinforcement of	GP verifies presence of identified risks and problems (as described in HRA-O summary report)
HRA-O by GP	Patient discusses recommendations of participant feed-back report with their GP (opportunistically at GP-patient encounter)
	GP motivates the patient to favourably change health behaviour and use recommended preventative care (opportunistically at GP-patient encounter)
Additional site-specific	London: GP gets reminders of identified risks and problems in EMR
reinforcement	Hamburg: Participants are offered one group session by interdisciplinary team or two home visits by nurse
	Solothurn: Participants are offered six-monthly home visits by health nurses over a two-year period

HRA-O: Health Risk Appraisal for Older Persons

PRO-AGE: PRevention in Older people – Assessment in GEneralists' practices

GP: General practitioner

EMR: Electronic medical record

#### Training of health professionals

GPs (and practice nurses in London) allocated to training were trained in risk identification, health promotion and prevention in older persons. This included initial (duration about 2 hours) and follow-up (every two to three months) interactive training group sessions in risk and problem identification, and in prevention and health promotion for older persons. Training sessions were led by one of the project physicians with expertise in preventative geriatric medicine. GPs were updated on emerging evidence, health promotion and preventative messages were reinforced, difficulties encountered as part of the study raised, and problem solving strategies discussed. As a reference guide, an evidence-based training manual was developed. This manual explained the HRA-O approach, and contained current preventative care recommendations for each of the domains included in the HRA-O with relevant literature related to the management of each of the domains and references supporting the recommendations made to both participants and their physicians [see Additional file 1]. This manual was also used as a basis for training of the other health professionals involved in the intervention.

#### Use of HRA-O instrument

The intervention is based on the HRA-O instrument consisting of a self-administered HRA-O questionnaire, a personalised feed-back report to the older person and a summary feed-back report for the GP or the health educator. The development, practicability and performance of the HRA-O questionnaire are described in a separate publication [7]. Briefly, the HRA-O questionnaire contains the following sections: Administrative information (name, address, date of birth, date of completion, completion time); self-reported chronic conditions, preventative care use, medication use, signs and symptoms, self-perceived health, physical activity, nutrition, injury prevention, tobacco use, alcohol use, eyesight, hearing, depressive symptoms, self-reported memory, social network, social support, basic and instrumental activities of daily living, socio-economic information (education, occupation, living arrangement, and selected additional items at each site, such as information on state pension in London), and health measurements (weight, height, blood pressure, cholesterol). In addition, it contains additional items based on the transtheoretical model of behaviour change, as a basis for addressing the participants' readiness to change and self-perceived barriers to changing health behaviour in the feed-back statements [13]. Completed questionnaires are entered into the computer, and an algorithm-based method automatically generates summary reports for the involved health professionals, as well as personalised feed-back reports for the participants. This includes individually tailored information and recommendations based on the older persons' responses to the questionnaire, general health information on each domain addressed in the HRA-O questionnaire, and sources of further information in the community.

In the PRO-AGE study, GPs or the study centre posted the approximately 34-page HRA-O questionnaire to all individuals allocated to the intervention arm and asked them to complete the questionnaire on their own or with the support of a proxy [7]. Participants who completed the HRA-O questionnaire and their health care providers received the computer-generated personalised feed-back reports generated by the study centre at each project site.

#### Reinforcement of HRA-O

GPs (and practice nurses in London) were encouraged to reinforce the HRA-O during usual encounters with their patients. GPs were encouraged to verify problems and risks identified with the HRA-O questionnaire, and to reinforce HRA-O based recommendations by motivating patients to change their behaviour, or by facilitating preventative care uptake. In addition, participant reports encouraged patients to discuss identified risks and written recommendations with their GP if necessary.

#### Additional reinforcement in London

London adopted a specific approach for using the provider summary report. From the physician summary report, participating GPs chose to enter all or some of the HRA-O feedback into the electronic patient record (EPR) using the Read code system, (a coding system used for the classification of medical problems in EPRs in the U.K.) [14]. This choice was made by the patient's usual GP, who marked the relevant sections of the provider feedback report and passed it to a data entry clerk. The information that the patient had completed the HRA-O questionnaire and had therefore received written recommendations was added as a reminder to the EPR, and in addition individual HRA-O identified risks were incorporated as reminders to the problem list of the EPR to act as electronic prompts when the record was accessed. Finally, the whole provider summary report was scanned into the EPR as if it were a hospital letter. It was left to the discretion of both providers and patients how HRA-O identified issues were addressed, be it directly, opportunistically during unrelated consultation, or not at all. Six months after receiving the feedback report, patients in the intervention group were sent a reminder card encouraging them to follow-up the recommendations in their report and consult the practice team if necessary.

#### Additional reinforcement in Hamburg

In Hamburg, all patients allocated to the intervention group were invited to participate in a 4-hour group session at a geriatric centre or to receive two home visits by a specially trained nurse [15-18]. Group sessions were given jointly by an interdisciplinary team consisting of a geriatrician, a physical therapist, a nutritionist, and a social worker working with a structured programme focusing first on successful aging, nutrition, preventative care, lifestyle modification, physical activity, medication use, social contacts, housing and living location and emphasising patient self-efficacy and empowerment. The second part of the group session covered nutrition and physical activity in more detail. The purpose was to encourage the setting of individual goals. In the third part of the group session participants received individual written recommendations from members of the interdisciplinary team [15,16]. Older persons who preferred home visits were offered two home visits (after base-line and at six months) by a specially trained nurse who conducted an additional multidimensional assessment of nutrition, medication use, pain, mobility, cognition, vision, and hearing, prioritised recommendations and follow-up for adherence with the recommendations [17,18].

#### Additional reinforcement in Solothurn

In Solothurn, all participants who returned the HRA-O questionnaire were offered home visits by specially trained health nurses. The nurses discussed the participant feed-back on the completed HRA-O questionnaire with the older persons, answered questions from patients, and conducted a detailed interview on physical activity and medication use in all patients. If needed, they conducted additional assessments in the areas of nutrition, medication use, pain, mobility, cognition, vision, and hearing. Nurses discussed each case with a project geriatrician, and subsequently with the GP. Recommendations were prioritised, reinforced or formulated in more detail (e.g., definition of specific recommendations related to physical activity), and if new risks were identified, new recommendations were formulated. Based on the transtheoretical model of behaviour change nurses attempted to achieve behaviour change by taking into account individual readiness to change and negotiating realistic goals with the older persons. Subsequently, nurses conducted follow-up visits at 6-monthly intervals, with interim phone calls to patients as needed over a two-year period. At one year, the nurses conducted a yearly assessment home visit based on the follow-up HRA-O and on additional assessments as needed. Further funding, secured once the project was underway, enabled the duration of the intervention to be extended to two years in Solothurn. This allowed longer-term follow-up of the effects of HRA-O combined with preventive home visits.

### Data collection

Prior to randomisation, participant age and gender were recorded from practice registers. Information on base-line self-perceived health status, prior health care use, and instrumental support were derived from the Pra questionnaire [10]. In addition, for the participants in London, the Townsend score [19], a measure of social deprivation based on indicators of the older person's living location, was derived from the participants' address information.

At the one-year follow-up, surviving participants of all groups (intervention, control, and concurrent comparison group) were sent a HRA-O questionnaire with additional questions on health care use [10] and on patient self-efficacy [20]. This follow-up questionnaire included all items required for outcome analysis, as listed in Table 2. In addition, the one-year follow-up questionnaire was used for obtaining information on socioeconomic information and self-reported chronic conditions among participants in the control and concurrent comparison groups. No reminders were sent to persons not returning this questionnaire. To reduce the amount of missing information on preventative care in the London sample, practices were asked to review patient medical records for information on preventative care use (vaccination coverage, blood glucose and cholesterol measurement, colon cancer screening) for patients who had returned the 1-year follow-up questionnaire but had incomplete information on some items of preventative care (n = 44 intervention group, n = 33 control group, n = 20 concurrent comparison group).

**Table 2 T2:** List of primary outcomes used in the PRO-AGE study at the follow-up: health behaviour and preventative care use

**Domain**	**One-year outcome analysis (all sites)**	**Two-year outcome analysis (Solothurn only)**
**Health behaviour**		
-Accident prevention	Driving without using seat belt [22]	Driving without using seat belt [2]
-Alcohol use	Possible hazardous or harmful alcohol use: based on age-and gender-specific limits of quantity and frequency of use [23]	Possible hazardous alcohol use: ≥ 2 drinks/day [2]
-Nutrition intake	Consumption of >2 high-fat food items per day [24]	Daily consumption of high-fat food items [2]
	Consumption of <5 fruit/fibre items per day [24]	Less than daily consumption of fruit and fibre items [2]
-Physical activity	Moderate or strenuous activity < 5 times/week [25]	Physical activity < 5 times/week [2]
-Tobacco use	Current tobacco use [5]	Current tobacco use [2]

**Preventative care use [21]**		
-Blood pressure	Self-report: blood pressure control in previous year	Medical record: blood pressure control in previous year
-Breast cancer screening	Self-report: mammography in previous 2 years	n.a.
-Cholesterol	Self-report: cholesterol measurement in previous 5 years	Medical record: cholesterol measurement in previous 5 years
-Colon cancer screening	Self-report: faecal occult blood test in previous year	Medical record: faecal occult blood test in previous year
-Dental care	Self-report: dental check in previous year	n.a.
-Diabetes screening	Self-report: blood glucose measurement in previous 3 years	Medical record: blood glucose measurement in previous 3 years
-Hearing examination	Self-report: hearing check-up in previous year	n.a.
-Influenza immunisation	Self-report: influenza vaccination in previous year	Medical record: influenza vaccination in previous year
-Pneumococcal immunisation	Self-report: pneumococcal vaccination (ever)	Medical record: pneumococcal vaccination (ever)
-Vision examination	Self-report: vision check-up in previous year	n.a.

PRO-AGE: PRevention in Older people – Assessment in GEneralists' practices

n.a. denotes not available

In Solothurn, in addition to the one-year follow-up, a two-year follow-up was conducted among persons in the randomised study (not in the concurrent comparison group). Health behaviour outcome data were collected using a two-page questionnaire based on the Healthtrac questionnaire [2]. In addition, older persons were asked for their self-perceived health status, and for need for help in basic activities of daily living. Non-responders or those who returned incomplete questionnaires, were contacted by telephone, or visited at home, and a trained research assistant, blinded for group allocation, attempted to obtain missing information. Selected preventative care measures (those mainly offered by GPs, and not by specialists, in the Swiss health care system) and selected health measurements (most recent values of blood based measurement, serum cholesterol, and serum glucose) were obtained from a review of primary care medical records. This abstraction of medical records was conducted by practice assistants based on an alphabetised list of participating patients blinded for group allocation.

At all sites, survival status and move into permanent long term care among non-responders at follow-up was obtained from GPs, and if available from registers in participating regions. Move into permanent long-term care was defined as living in a nursing home in London and Solothurn, and in Hamburg as requiring nursing care according to the German long-term care insurance system.

At the end of the follow-up period (London and Hamburg, at one-year follow-up, Solothurn at two-year-follow-up), participating GPs and other health personnel involved in the HRA-O intervention, received a structured, uniform questionnaire for written feed-back on the project.

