### Randomisation of participants

Participating patients of GPs who had received the training were randomly allocated to intervention and control groups by the independent study centre using a computer generated allocation sequence. People living in the same household were allocated to the same group. The ratio of allocation of participants to intervention and control groups was 1:1 in the London sample and 1:2 in the Hamburg sample. In the Solothurn sample, a 1:1 randomisation ratio was used in the initial study phase, and then changed to 1:2, resulting in an average ratio of 1:1.6. Variation in randomisation rates was related to budgetary constraints (see sample size calculation), which became apparent after the project was underway. Participants allocated to the intervention group were offered HRA-O with personal reinforcement. Those allocated to the control group received usual care.

Participants of GPs who had not received additional training formed the concurrent comparison group. All patients in this group continued to receive usual care during the study period. GPs in this group received only general project information during the study period, and were offered the training after the end of the project follow-up.

Final inclusion of study participants started in November 2000 and was completed in London in October 2001, in Hamburg in September 2001, and in Solothurn in February 2002.

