### Statistical analyses

All analyses follow an a priori analytic plan. The primary outcomes are health behaviour and preventative care use, as listed in Table 2[2,5,21-25]. Secondary outcomes include mortality, need for long-term care (living in nursing home, or designated as requiring long-term care according to the German long-term care insurance system), and self-reported information on health status (vision, hearing, self-perceived health status, pain, depressive symptoms, falls history, and functional status).

To conduct planned sensitivity and subgroup analyses of primary outcomes, two composite scores will be created: one for adherence to positive health behaviour, and one for use of recommended preventative care. The percentage of health behaviour domains (Table 2) for which the patient showed a positive level of performance, and the percentage of recommended preventative care measures (Table 2) the patient had used will be determined. We will impute composite scores for individuals in whom ≤ 20% of the required outcome data were missing. Imputation will be conducted as follows: based on available baseline variables multiple linear regression models (using the complete base-line information and household status) will be derived in the subset of persons with complete data on outcomes, and subsequently, these models will be used to impute composite score estimates in persons with missing information.

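### In Hamburg and Solothurn some intervention participants have vision and hearing assessed by a study nurse, and the self-reported vision and hearing check-up outcomes name no provider, so the treatment itself may be counted as an outcome

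*Protocol article*

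**What the plan says.** **Outcomes.** The Statistical analyses section states: "The primary outcomes are health behaviour and preventative care use, as listed in Table 2". For the one-year analysis at all sites, Table 2 lists "Self-report: hearing check-up in previous year" and "Self-report: vision check-up in previous year". Neither entry gives a provider or setting. Both are among the ten preventative-care measures behind the composite, which is the percentage of recommended measures a person has used.

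**Hamburg.** Intervention participants were offered a group session or nurse home visits. On the visits, the article says: "Older persons who preferred home visits were offered two home visits (after base-line and at six months) by a specially trained nurse". This nurse "conducted an additional multidimensional assessment of nutrition, medication use, pain, mobility, cognition, vision, and hearing". Vision and hearing are not among the topics listed for the group session.

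**Solothurn.** Nurses visited participants who had returned the HRA-O questionnaire. In the account of the initial visit: "If needed, they conducted additional assessments in the areas of nutrition, medication use, pain, mobility, cognition, vision, and hearing". After that, "nurses conducted follow-up visits at 6-monthly intervals", and no vision or hearing content is described for those visits. Assessments as needed appear again at the one-year visit, which builds on the follow-up HRA-O.

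**Controls.** "Those allocated to the control group received usual care".

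**Analyses.** Composites serve the sensitivity and subgroup analyses. For Hamburg and Solothurn, they are also regressed on participation in the reinforcement, controlling for allocation and baseline characteristics, to estimate the reinforcement's independent effect.

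**The concern.** The trial asks whether HRA-O with reinforcement raises the use of recommended preventative care. At two sites, part of the reinforcement is an activity that a participant could reasonably describe as a vision or hearing check-up. A control cannot acquire a yes by this route. A difference in these two items could therefore partly show that the nurse came, and not that the participant obtained an eye or ear examination elsewhere.

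The reinforcement regression is the most exposed analysis. Where reinforcement means the nurse visit, the exposure and part of the outcome can be the same event.

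Nothing planned would reveal this:

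- The London record review covers other items and another site.
- Both items are unavailable in the record-based two-year Solothurn analysis.
- The sensitivity analyses address missing data.
- The Discussion covers self-report, missing data, power and contamination, but not this overlap.

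**Working it through.** **1. The plan's design effect.** The Sample size section gives 20% prevalence in controls, a 30% difference, two-sided 0.05, 80% power and 20% drop-out. Read as relative, the target is 0.20 × 1.30 = 0.26, a 6-point difference. A two-proportion formula with continuity correction gives 805 evaluable per group at 1:1, and 805 / 0.80 = 1007 enrolled (stated: 1000). At 1:2 it gives 596 and 1192 evaluable, so 745 and 1490 enrolled (stated: 763 and 1525). All are within 3%. An absolute 30-point difference would need only 39 to 45 per group, so the relative reading is the plan's. The sample size is not in dispute; 6 points is used below as the yardstick.

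**2. Who can be exposed, and when.**

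| Site | Nurse assesses vision and hearing in | Timing against the one-year look-back |
|---|---|---|
| London | nobody (reminders in the medical record) | none |
| Hamburg | those who chose home visits | after baseline and at six months; the later visit is well inside |
| Solothurn | those in whom it was needed | initial visit, near the edge of the window; the one-year visit follows the outcome questionnaire |

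**3. Effect on one item.** Let p0 be the prevalence without the visit. Let f be the share of the whole intervention arm who were assessed by the nurse and report it as a check-up. With no true effect on outside check-ups, and assessment independent of them:

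apparent rate = p0 + (1 − p0) × f

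The article does not give f, so a range is shown. The value p0 = 20% is the plan's general planning figure, not one for vision or hearing. The chance of a significant result assumes 80% of those enrolled are evaluable (Hamburg 878 vs 1702 enrolled, Solothurn 874 vs 1410), two-sided 0.05, and ignores household clustering.

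| f | Apparent rate | Excess | Chance of significance, Hamburg | Solothurn |
|---|---|---|---|---|
| 2% | 21.6% | 1.6 points | about 14% | about 13% |
| 5% | 24% | 4 points | about 56% | about 52% |
| 7.5% | 26% | 6 points | about 87% | about 85% |
| 10% | 28% | 8 points | about 98% | about 97% |

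The f that reproduces the design effect is 0.06 / 0.80 = 7.5%. At p0 = 40% it is 0.06 / 0.60 = 10%.

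**4. Effect on the composite.** For a person in whom both items change from no to yes, the score rises by 2/10 = 20 points, or 2/9 = 22 points if mammography does not apply. Averaged over the arm, with both items changing and p0 = 20%, the rise is 0.20 × 0.80 × f. At f = 10% that is 1.6 points, which is modest.

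**5. Effect on the reinforcement regression.** Only people who were visited can report the visit. If a share v of the intervention arm had nurse visits, the fraction affected among them is f / v, which is never below f. The model controls for allocation, so it sets participants against non-participants within the intervention arm. The artefact is thus at least as large here as in the arm comparison when participation means nurse visits. In Hamburg, counting group-session attenders as participants would dilute it.

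**The case against.** **The questionnaire is not shown.** Table 2 gives labels, and the item wording is in a separate publication that may exclude nurse assessments. The measures taken from Swiss GP records are described as those mainly offered by GPs and not by specialists. Vision and hearing were not among them, which hints that specialist examinations were meant. This stands, and it lowers confidence. But the sentence explains the record review and does not define the self-report item.

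**Exposure is partial.** A reader might infer that the whole intervention arm at both sites was assessed, or that every six-monthly Solothurn visit included vision and hearing. The text does not support either. Hamburg exposure is limited to those who preferred home visits. In Solothurn the assessment depends on need and is described for the initial visit.

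**The reporting step is assumed.** The article does not say whether the assessment was an interview, a screen or a test, or whether people would call it a check-up. Those assessed because of a problem may already see a specialist, so the nurse's visit would change fewer answers than the independence formula implies. Both points stand and limit the size.

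**It may be intended.** Facilitating preventative care is an aim of the package, so care delivered by the nurse could be counted as care use. That is defensible if stated, but then the items do not measure uptake outside the study visits.

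**Dropping the items would be disproportionate.** Taking two prespecified primary outcomes out at two sites invites the charge of selective reporting, and the questionnaire has already been fielded. This stands, and the fix below does not do it.

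**Conclusion.** The overlap between intervention content and outcome is in the text, and no planned analysis addresses it. The conclusion is conditional: the one-year comparisons of these two items, the preventative-care composite and above all the reinforcement regression in Hamburg and Solothurn can be biased toward benefit. A reader might go further and take the bias as established; the article does not support that, because f and the item wording are unknown.

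At 20% prevalence without the visit, the excess on an item is 1.6 points at f = 2% and 6 points at f = 7.5%. These figures rest on no true effect on outside check-ups and on independence between nurse assessment and outside check-ups. The effect on the arm-level composite is much smaller. The other primary items, London and the two-year analysis are not touched by this point. It deserves a change to the analysis and its interpretation, but it does not threaten the trial as a whole.

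**What to change.** Keep both items as prespecified primary outcomes. For the one-year analysis in Hamburg and Solothurn:

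- If the questionnaire answers identify the provider, do not count assessments by study nurses as check-ups.
- If they do not, run the preventative-care composite and the regression on participation in the reinforcement twice, with and without the vision and hearing items, and report both.
- State in the plan that a difference in these two items alone will not be read as evidence of uptake of care outside the study visits.

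This needs no new data and no change in sample size. The outcome analyses are still described in the future tense, so the statement can be made in advance. The cost is a little more analysis and a more cautious conclusion on two items at two sites.
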